### Sample size

This being a feasibility study, we do not provide a power calculation as there is no proposal for formal hypothesis testing, and the sample size focuses on the required precision of feasibility parameters in line with recommendations for pilot and feasibility studies.^21^ FEP has a relatively low incidence of about 26.6 per 100 000 person-years.^22^ In order to obtain an adequate sample size to measure feasibility outcomes, we will include all UCs in district Peshawar (n=93) in the sample, allocated to ETAU and THE HOPE arm in a 1:1 ratio. We will aim to recruit a minimum of 90 patients (45 in each arm) over a 12-month period. We believe this will help us to achieve reasonable precision of feasibility estimates, for example, for evaluation of intervention fidelity and participant retention in the study (as a proportion). This will enable the 90% one-sided lower confidence bound to be derived to a margin of error of 0.1 for single-arm evaluation and 0.07 for overall sample evaluation. This fits the criteria for sample size justification and calculation recommendations for pilot and feasibility studies.^23^

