### Participant eligibility criteria

We will recruit patients (aged 14–25 years) residing in one of the UCs in district Peshawar with first ever psychotic episode who have not received antipsychotic medication previously, or if they already have used antipsychotic medications, it was for no longer than 6 weeks.^28^ The FEP diagnosis will be made at an interview by psychiatrists based on the International Classification of Diseases, 11th revision (ICD-11) criteria for schizophrenia, persistent delusional disorder, acute and transient psychotic disorders, schizoaffective disorder, mood disorders (mania, severe depressive episode, bipolar affective disorder) with psychotic symptoms.

The exclusion criteria will be: (1) evidence of overt learning disability; (2) organic brain damage or pervasive developmental disorder; (3) severe substance abuse (except nicotine dependence); and (4) a young person or parent not willing to provide informed consent.

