#### Quantitative data collection and follow-up

Once the participant has provided informed consent, trained RAs will collect the demographic information and complete baseline assessment and suicide risk screen based on the MhGAP intervention guide. Follow-up data will be collected 12 weeks post-baseline by the RAs blinded to the allocation status.

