###### Secondary outcome measures

In addition to feasibility outcomes, the study will aim to measure a range of clinical outcomes and service utilisation measures for assessing the feasibility and acceptability of the intervention. In addition, process evaluation (see below) will be done using qualitative methods. Table 1 provides details of these outcomes and the baseline and follow-up points for these assessments.

**Table 1 T1:** Data collection schedule and list of assessments

Description	Measure	Screening assessment	Baseline assessment	4 weeks post-baseline	3 months post-baseline
Age	Date of birth	✓			
Gender	Male/female	✓			
Education	Years spent in education	✓			
Marital status		✓			
Work status		✓			
Psychopathology	Brief Psychiatric Rating Scale^31^		✓		✓
	Young Mania Rating Scale^32^		✓		✓
	Hamilton Depression Rating Scales^33^		✓		✓
	Clinical Global Impression Scale^34^		✓		✓
Occupational and social functioning	Global Assessment of Functioning^35^		✓		✓
Duration of untreated psychosis	Comprehensive Assessment of At-Risk Mental States^36^	✓			
Quality of life	EuroQol-5^37^		✓		✓
Family burden	Perceived Family Burden Scale^38^		✓		✓
Perceived stigma	Internalised Stigma of Mental Illness^39^		✓		✓
Physical health	Weight and body mass index		✓		✓
Substance abuse	Drug Abuse Screening Tool^40^		✓		✓
Response to antipsychotic treatment	Brief Psychiatric Rating Scale^31^			✓	
Adherence to antipsychotic treatment	Medication Adherence Rating Scale^41^				✓
Rates of disengagement	Response to contact requests for a consecutive 4-week period during follow-up				✓
Remission rates	Score of 3 or below on the Brief Psychiatric Rating Scale,^31^ maintained at least for 3 months		✓		✓
Service utilisation metrics	indicated by: Number of TSHs approached, consented and completed the training programme Patients screened for suspected psychosis Total number of confirmed cases	✓	✓		✓
The acceptability of trial procedures	Adherence to trial procedures and completion of the assessments at baseline and 12 weeks		✓		✓
Fidelity of intervention	First-Episode Psychosis Services Fidelity Scale, modified and adapted for the local settings^43^		✓		✓
Implementation costs	The Client Service Receipt Inventory^44^		✓		✓

TSHs, traditional and spiritual healers.

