**Psychopathology:** Brief Psychiatric Rating Scale (BPRS),^31^ Young Mania Rating Scale,^32^ Hamilton Depression Rating Scale,^33^ and Clinical Global Impression Scale^34^ for measuring improvement in symptoms and remission rates.**Functioning:** Global Assessment of Functioning.^35^**DUP:** Comprehensive Assessment of At-Risk Mental States at baseline.^36^**Quality of life:** EuroQol-5.^37^**Family burden**: Family Burden Scale.^38^**Stigma**: Internalised Stigma of Mental Illness.^39^**Physical health**: weight and body mass index.**Substance abuse**: Drug Abuse Screening Tool.^40^**Response to antipsychotic treatment:** change in BPRS^31^ from baseline to 4 weeks after starting antipsychotics.**Adherence to antipsychotic treatment:** Medication Adherence Rating Scale.^41^**Rates of disengagement** are defined as a participant’s refusal to engage with treatment or not responding to contact requests for a consecutive 4-week period during follow-up while still residing within the study site catchment area.^42^**Remission rates:** improvement in psychotic symptoms from baseline (operationalised as a score of 3 or below on the BPRS^31^), maintained for 3 months.**Service utilisation metrics** measures will be used as a measure of the acceptability of the intervention. These will include patients screened for suspected psychosis out of all those presenting to at different contact points, the median time taken in screening, frequency and duration of contacts, the median length of time to treatment from assessment to starting treatment, the proportion of cases identified as at-risk mental state for FEP out of total accepted cases and the willingness of TSHs to work with health services (indicated by the number of TSHs approached, consented and completing training programme).**The acceptability of trial procedures** will also be assessed through adherence to trial procedures and completion of the assessments at baseline and 12 weeks.**Fidelity of intervention:** FEP Services Fidelity Scale, modified and adapted for the local settings,^43^ will be used to assess the degree to which mental health teams deliver evidence-based care for FEP.**Implementation costs:** the Client Service Receipt Inventory^44^ will measure direct and indirect costs in implementing the intervention to estimate health economic costs from the payer and provider perspective. We will estimate mean, median and quartile costs at each time point.

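### Remission is described as improvement from baseline but scored as an absolute BPRS level held for 3 months, which within a 12-week schedule only patients already at that level at baseline can document

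*Protocol article*

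**What the plan says.** All of this is in the protocol article.

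- **Secondary outcome measures, text.** Remission is "improvement in psychotic symptoms from baseline (operationalised as a score of 3 or below on the BPRS", followed by a condition that it be maintained for 3 months.
- **Table 1, remission row.** The measure is "Score of 3 or below on the Brief Psychiatric Rating Scale", "maintained at least for 3 months". The row mentions neither baseline nor change. It is ticked at baseline and at 3 months.
- **Table 1, BPRS.** The scale is scheduled at baseline and 3 months under psychopathology, and at 4 weeks under response to antipsychotic treatment.
- **Quantitative data collection and follow-up.** "Follow-up data will be collected 12 weeks post-baseline by the RAs". This is the visit that Table 1 labels 3 months.
- **Participant eligibility criteria.** Entry rests on a diagnosis: "The FEP diagnosis will be made at an interview by psychiatrists". No BPRS or other severity score is required. Patients with earlier treatment may enter: "if they already have used antipsychotic medications, it was for no longer than 6 weeks".
- **Secondary outcome measures, response.** Response to antipsychotics, by contrast, is defined as a BPRS change "from baseline to 4 weeks after starting antipsychotics".

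**The concern.** The description and the rule are not the same quantity. The description requires a patient to get better than at entry, whereas the rule asks only where the patient stands. The two agree if everyone starts above the threshold, but nothing in the eligibility criteria ensures that, and admitting patients with some prior antipsychotic treatment makes exceptions possible. Such patients have nothing to remit from on this scale, yet they enter the denominator and, if unchanged, the numerator.

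The maintenance condition does not screen them out, because a score that is low throughout meets any duration. It works against patients who do improve, since the follow-up is too short for them to show 3 months at the new level.

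What is at stake is what the remission rate means. The objectives include benchmarking outcome measures and supporting sample size calculation for a later trial, and the Quantitative analysis section plans to identify the outcomes most sensitive to change. A rate that partly or wholly reflects baseline status is a poor guide for either purpose.

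**Working it through.** The protocol states no remission rate, no baseline BPRS distribution and no sample size based on remission, so there is no figure to reproduce. The check has two parts.

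**1. What the schedule can document**

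- Baseline to last visit: 12 × 7 = 84 days. Table 1 treats this as 3 months. A calendar quarter is 365.25 / 4 = 91.3 days, so even this span is only about 3 months.
- 4-week visit to last visit: 84 − 28 = 56 days.

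| BPRS at baseline | 4 weeks | 12 weeks | Longest documented spell at 3 or below | Crossed the threshold? |
|---|---|---|---|---|
| ≤3 | ≤3 | ≤3 | 84 days | No |
| >3 | ≤3 | ≤3 | 56 days | Yes |
| >3 | >3 | ≤3 | 0 days (one reading) | Yes |

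Only the first row reaches about 3 months. The result does not depend on the exact date of the middle visit. The text ties that visit to the start of antipsychotics and Table 1 ties it to baseline, but any visit after baseline leaves fewer than 84 days.

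**2. What the rule counts (illustration only)**

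Let q be the share at 3 or below at baseline, s the share of those still there at 12 weeks, and r the share of the others who are at 3 or below at 12 weeks. The documents give none of these, so all values are assumptions. The sample is the planned minimum: "We will aim to recruit a minimum of 90 patients (45 in each arm".

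One way to motivate q is the share with prior antipsychotic treatment times the share of those already at the threshold: 0.25 × 0.2 = 5%; 0.25 × 0.4 = 10%; 0.5 × 0.4 = 20%. A value of q = 0 is equally compatible with the documents.

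Patients counted without improving = 90 × q × s:

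| q | s = 0.8 | s = 1.0 |
|---|---|---|
| 0% | 0 | 0 |
| 5% | 3.6 | 4.5 |
| 10% | 7.2 | 9.0 |
| 20% | 14.4 | 18.0 |

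Rates at q = 10%, s = 1.0, r = 30%:

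- Loose reading (3 or below at the last visit is enough): q·s + (1 − q)·r = 0.10 + 0.90 × 0.30 = 0.37.
- Strict reading (about 3 months must be documented): at most q·s = 0.10, all of it from patients who never crossed the threshold. At q = 0 it is 0.
- Patients already at 3 or below removed from the denominator, status at 12 weeks: r = 0.30.
- The same patients kept and counted as not remitted: 0.90 × 0.30 = 0.27.

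On these inputs the same data give 10%, 27%, 30% or 37%, depending on how one sentence is read.

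**The case against.** The strongest reply is that the sentence should be read as a whole: the patient must improve from baseline and also reach 3 or below, so a patient at 3 on both occasions does not qualify. Handling of patients already at the threshold would then be a detail for the analysis plan. This does not fit the wording. The parenthesis says how improvement is operationalised and does not add a second condition; Table 1 gives only the absolute score; and the response outcome shows that change is stated where change is meant. An operational definition given in the article is also not a detail left for later.

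Other points stand:

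- An absolute threshold is an acceptable way to define remission. The fault is its mismatch with the description and with the follow-up.
- The baseline tick in Table 1 may only schedule the reference score. It does not show that baseline scores are meant to count as remission.
- Entry requires a diagnosed first psychotic episode, so few patients, or none, may start at 3 or below.
- Restricting the denominator without touching the maintenance clause would give a rate of zero by construction, since nobody starting above 3 can document 3 months.
- Patients are recruited after clusters are randomised, so baseline BPRS may itself differ by arm. Restricting on it selects patients and can introduce bias of its own.

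A reader might also infer that the remission rate will be materially inflated, that the arms will differ for this reason, or that the decision to proceed is at risk. The documents support none of these. They give no baseline scores, they do not say that remission will be the outcome used to size the main trial, and the red, amber and green criteria use recruitment, follow-up and healer participation only.

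**Conclusion.** The point holds as a defect of definition. Remission as written can be met without improvement. Read strictly against the visit schedule, it can be documented only by patients already at 3 or below at baseline and by nobody who crosses the threshold afterwards. The second conclusion needs only the protocol's own visit times and no assumed figure.

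The size is unknown. The illustrative 3.6 to 18.0 patients out of 90 rest wholly on assumed q of 5% to 20% and s of 0.8 to 1.0, and the number is 0 at q = 0. The text also does not say whether the score of 3 applies to each item, to selected items or to a total. The finding holds on any reading under which a patient can be at 3 or below at baseline.

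The consequence is limited to one secondary outcome in a feasibility trial without formal hypothesis testing, and to its use in choosing and sizing outcomes for a main trial. The definition should be corrected before analysis; the trial's feasibility conclusions do not depend on it.

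**What to change.** Make these changes in one edit to the outcome definition and the Table 1 row:

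1. State which BPRS items the score of 3 or below covers.
2. Report remission among participants above 3 on those items at baseline. Show the number at 3 or below at baseline per arm, and give the all-participant rate alongside. Both rates are needed because recruitment follows cluster randomisation and baseline status may differ by arm.
3. Reconcile the 3-month maintenance clause with the 12-week follow-up, for example by reporting symptomatic remission status at 12 weeks without claiming 3 months' maintenance. Step 2 is not usable without this step.

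The cost is wording and one extra table row, since BPRS is already collected at baseline and 12 weeks. The downsides are a slightly smaller denominator for the restricted rate and a renamed or less favourable outcome. If maintenance is dropped, the result describes status at one time point and should be labelled so.

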##### Blinding and allocation concealment

It is not possible to blind study participants from their treatment arm allocation. However, the assessment team conducting the baseline and follow-up assessments will be blinded to the treatment arm of the cluster. During all assessments, the key feasibility outcome measures will be completed first to minimise the risk of bias in the event of unblinding, and if it occurs, the point of unblinding will be recorded. Sensitivity analyses will be carried out to assess the effect of unblinding on the clinical outcomes. The trial statistician will be blind to allocation status. The psychiatrist diagnosing FEP will be blind to the diagnosis given by PCPs and the impression of illness by TSHs. This will help to minimise the bias and provide a good measure of training intervention.

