### Study procedures and data collection

The RA will refer all suspected cases from TSHs and PCPs to the psychiatrists assigned to each arm, who will independently assess patients within 48 hours of referral, being blind to the diagnosis (by PCPs) or impression of TSHs. The ‘diagnosis’ of FEP by TSHs will be recorded using an instrument developed in consultation with TSHs. This instrument will indicate the likelihood of a person suffering from FEP, as judged by the TSH. Separately, TSHs will also be asked to identify the lay terminology they use in their routine work to capture their conceptualisation of FEP. For patients referred from primary care, PCPs will be asked to provide the likely diagnosis based on ICD-10 (see figure 2).^30^

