##### Outcome measures

###### Primary outcome measures

Key feasibility outcomes for the trial will include the total number of cases recruited in the 12-month period and cases referred by TSHs and PCPs to psychiatrists with suspected FEP during the recruitment period. It will also include the number of FEP cases suspected by TSHs and PCPs and the likelihood of the confirmed diagnosis of FEP based on interview diagnosis by psychiatrists and DUP in those meeting criteria for FEP.

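### At the 12-week visit the unblinding safeguard covers none of the rater-scored scales, and the article does not separate research assistants who refer by arm from those who must be blind

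*Protocol article*

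**What the plan says.** Four parts of the protocol article bear on this.

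- **Referral** (Study procedures and data collection): "The RA will refer all suspected cases from TSHs and PCPs to the psychiatrists assigned to each arm".
- **Assessment** (Quantitative data collection and follow-up): at entry, "trained RAs will collect the demographic information and complete baseline assessment and suicide risk screen". Later, "Follow-up data will be collected 12 weeks post-baseline by the RAs blinded to the allocation status".
- **Blinding** (Blinding and allocation concealment): "the assessment team conducting the baseline and follow-up assessments will be blinded to the treatment arm of the cluster". The safeguard against loss of blinding is an ordering rule: "During all assessments, the key feasibility outcome measures will be completed first to minimise the risk of bias in the event of unblinding". The section adds that the point of any unblinding is recorded and that sensitivity analyses will examine its effect on the clinical outcomes.
- **Outcomes put first** (Primary outcome measures). The list begins: "Key feasibility outcomes for the trial will include the total number of cases recruited in the 12-month period and cases referred by TSHs". Referrals by PCPs count as well. Next come the number of suspected cases, and then "the likelihood of the confirmed diagnosis of FEP based on interview diagnosis by psychiatrists and DUP in those meeting criteria for FEP".

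Table 1 and the list of secondary outcomes place BPRS, Young Mania, Hamilton, CGI and GAF among the secondary measures, at baseline and 3 months. DUP is obtained with the Comprehensive Assessment of At-Risk Mental States. Table 1 ticks it at screening, and the text says baseline. It is not repeated at follow-up.

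**The concern.** Two things look wrong.

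First, a person who sends each case to the psychiatrist of the right arm will probably know the arm. The article uses the same role name, RA, for this task and for the assessments that must be blind. Nothing in the text keeps the two tasks apart.

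Second, the ordering rule is meant to limit bias if blinding fails, and such bias enters through a rater's judgement. The measures given priority are mostly counts that no assessor scores at an interview. The scales that do depend on judgement are not in the priority group.

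What is at stake is detection bias in the clinical estimates. Under Quantitative analysis, the plan calculates means and confidence intervals within and between groups, judges which outcome responds most to change, and derives parameters for sizing the main trial. Bias that acts on rater-scored scales more than on self-report could distort both that choice and that sizing.

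**Working it through.** No arithmetic applies: the point uses no sample size, error rate or effect size. The check sets the passages side by side.

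**Step 1. Who knows the arm, and who must not.**

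| Task | Done by | Knowledge of arm |
|---|---|---|
| Routing suspected cases from TSHs and PCPs | The RA | Probably needed, since psychiatrists are assigned by arm |
| Baseline assessment | Trained RAs | Must be blind |
| 12-week assessment | RAs | Must be blind |

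The role name is shared and no separation is stated. The article also does not say that the same individuals do both tasks. The proportion of TSH- or PCP-referred participants rated by someone who routed them therefore cannot be determined. It could be none or all.

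**Step 2. What the ordering rule protects at each time.**

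| Primary feasibility outcome | Source | Rated at entry? | Rated at 12 weeks? |
|---|---|---|---|
| Cases recruited, referred, suspected | Counts | No | No |
| Confirmed FEP diagnosis | Psychiatrist's interview | Yes, by the psychiatrist | No |
| DUP | Structured assessment at screening or baseline | Yes | No |

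At entry the rule has a use: it can protect DUP, a primary outcome that needs judgement. At 12 weeks the last column is empty, so completing these measures first protects no rated measure. Of the five rater-scored scales taken at that visit, the rule gives priority to none. The 4-week column of Table 1 holds only the BPRS, so order does not matter there.

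**Step 3. Where the plan itself sees the risk.** The sensitivity analyses for unblinding concern the clinical outcomes, so the plan recognises that these are the measures at risk. The ordering rule does not put them first.

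**Step 4. What depends on the rated scales.** The red, amber and green criteria use recruitment, completion of follow-up visits, and TSH consent, training and referral work. None uses a rated scale. The between-group clinical estimates and the choice of outcome for the main trial do.

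**The case against.** The strongest reply has four parts.

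1. *The same-person reading is an inference.* A reader might conclude that the RAs who must be blind are the ones who route patients, and so are unblinded from referral. The documents do not support that. The wording on follow-up can be read as a specified subset of RAs, the blinding section speaks of an assessment team, and Recruitment mentions an independent researcher. Allocation of tasks may sit in standard operating procedures. This stands. What remains is that the stated duties are not reconciled.

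2. *The rule is not idle throughout.* A reader might say that the measures completed first need no rater. That is wrong for the whole set, because DUP and the confirmed diagnosis need judgement at entry. This stands too, and it confines the criticism of the rule to the 12-week visit.

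3. *The rule is not shown to do harm.* A reader might infer that adherence, contact or service-use questions come ahead of the scales and so reveal the arm. No passage sets that order, and those items are listed as secondary, alongside the scales. At follow-up the rule fails to protect, which is different from causing unblinding.

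4. *The plan has mitigations and is candid.* It records unblinding, plans sensitivity analyses, and concedes under Limitations that assessors' blindness may not hold. It proposes no formal hypothesis testing. These points lower the stakes. But recording and sensitivity analysis describe bias after the fact. They also have less to work with if few blinded ratings remain for comparison.

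**Conclusion.** The point holds in a limited form. At the 12-week visit the ordering rule protects none of the five rater-scored scales, because no primary feasibility outcome is rater-scored at that visit. At entry the rule can protect DUP and should stay. Separately, the duty to refer by arm and the duty to remain blind stand unreconciled in the article.

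The consequence falls on secondary but useful results: the between-group clinical estimates and the choice and sizing of the main trial's outcome. The decision to progress is largely unaffected. The size of any bias cannot be estimated from the article, since neither the number of RAs nor their division of work is given.

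The verdict assumes that the key feasibility measures in the blinding section are those listed under Primary outcome measures, and that the five scales are scored by the RAs who carry out the assessments. The change is cheap and acts on a rule already in the plan, so it should be made.

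**What to change.** Amend the blinding section and reconcile it with the section on study procedures:

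- At screening and baseline, keep DUP first.
- At follow-up, complete BPRS, Young Mania, Hamilton, CGI and GAF first. Leave adherence, service-receipt, contact and pathway items until last, since the answers could reveal the arm.
- State that, within the existing RA team, an RA who refers a patient does not rate that patient.
- State that assessors are not told the referral source or the assigned psychiatrist.
- Keep the recording of unblinding and the sensitivity analyses as they are.

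The cost is a change of wording in the protocol and operating procedures, and a small loss of flexibility in scheduling RAs. The role split needs more than one RA to be available for each patient's pathway. The article refers to RAs in the plural but gives no number, so this must be confirmed.
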